**Parties involved**

Radboudumc, Erasmusmc, BBMRI, Perined, PALGA, ZorgTTP, CBS

**Changes in the plan:**During data-preparation
- We decided to exclude all multiple pregnancies (twins, triplets etc)
**-** We decided to include women with only treatment after the pregnancy, but biopsy-proved CIN before the pregnancy in group 1 (untreated CIN)
- We decided to only use the spontaneous births for our analysis
- We could not adjust for all potential confounders, as not all these data was (well) documented in Perined, such as smoking, BMI, immunosuppressive drug use, sexual behavior and socio-economic status
- We could only calculate the size of the excised volume for a select group of women, as the macroscopic description was not always (in three dimensions) identifiable. We could, therefore, not use this variable in the main multivariate analysis.
During data-analysis
- The two selected groups from PALGA were matched with a control group, but after linking this data with Perined and looking per pregnancy instead of per women the groups were not completely equal anymore based on these matching criteria. We therefore decided, for example, to also include ‘urbanization’ in the multivariate analysis.

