**Background**

Cervical cancer screening has been in place in the Netherlands for several decades. Aim of the screening program is to identify and treat premalignant cervical lesions before they progress to cancer. This has led to a strong reduction in cervical cancer incidence and mortality. However, the downside of this screening is unnecessary referral of many women without any abnormalities or lesions that only have very low risk of progressing to cancer. This downside is even more pronounced in the new screening program where high-risk human papillomavirus (hrHPV) testing has replaced primary cytology testing. Most high-risk cervical lesions but inevitably also many lesions with a lower risk are treated by large loop excision of the transformation zone (LLETZ). Various studies and meta-analyses point to an increased risk of perinatal complications such as preterm delivery, low birth weight, premature rupture of membranes and caesarean delivery after LLETZ treatment. Therefore, overtreatment of fertile women has main priority for policymakers. However, it is unknown whether this increased risk is only due to the excision procedure itself, to the underlying cervical intraepithelial neoplasia (CIN) or to secondary risk factors which are associated with both preterm birth and CIN. The purpose of this study is to investigate the association between untreated CIN, treated CIN and adverse obstetrical and perinatal outcomes.

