
- Age of women during cytology/biopsy/treatment
- Date of cytology/biopsy/treatment
- Number of biopsies/treatments
- Histologic diagnosis
- Macroscopic description to calculate the size/volume of the biopsy/treatment by a datamining
 procedure.
- Type of treatment cannot be further specified

**Perined selection**- Period: 01-01-2010 until 31-12-2018
- Pregnancies between 16-24 weeks could be in the database, but this is not required
- Pregnancies of 24 weeks and more are mandatory in the database

Maternal variables
- Conception (spontaneous or with medical help)
- General history
- Obstetrical history
- Gravidity
- Parity
- Singleton or multiple pregnancy (twins, triplets etc)
- Gestation in days and weeks
- Age of the mother at childbirth (calculation through date of childbirth and age at histology date?)
- Date of childbirth
- Start of delivery (spontaneous, iatrogenic)
- Way of delivery (spontaneous, assisted vaginal delivery, caesarean section)
- Presenting part during delivery
- Problems during current pregnancy

Neonatal variables
- Birth weight in grams
- Apgar score after 5 minutes
- Congenital diseases
- Admission after birth (high care, intensive care, post-ICHC; period of admission in days)
- Perinatal death (gestation, antepartum/durante partu/postpartum)

Risk factors for preterm birth
- Ethnicity
- Smoking
- Immunosuppressive medication
- BMI
- General history: infectious diseases, auto-immune diseases, organ-transplantation, diabetes
 mellitus, epilepsy, psychiatric diseases, thyroid disorders
- Obstetrical history: curettage in history, history of abortion, history of preterm birth
- Short interval between pregnancies
- Conception through IVF/ICSI/egg donation
- Multiple pregnancy (twins, triplets etc)
- Nulliparous women
- Problems during current pregnancy: maternal infection, pre-eclampsia, gestational diabetes,
 placental problems
- Congenital diseases

Date of histology and date of childbirth will be used to make a selection of women who were treated before and after their pregnancy to additionally compare perinatal outcomes before treatment and after treatment.

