**Analyses**
Primary outcome
The odds ratio of premature birth (<28/<32/<37 weeks) will be calculated between the three groups
Secondary outcomes
Threatened premature birth, premature rupture of membranes, mode of delivery, low birth weight, admission to NICU, APGAR score, perinatal mortality
Sub analysis
Will be done for severity of grade, number of biopsies/treatments and size of biopsy and/or LLETZ
Confounders
There will be adjusted for potential confounders, such as gemelli pregnancy, premature birth in history, induction of labor, IVF/ICSI pregnancy, pre-eclampsia, diabetes mellitus, diabetes gravidarum, age, smoking, BMI, immunosuppressive drug use, congenital disorders, ethnicity etc.

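### Restricting the whole analysis to spontaneous births selects on how delivery began: the odds ratio no longer matches the planned preterm-birth outcome, can be biased in either direction, and covers only part of mode of delivery and perinatal mortality

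*Protocol*

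**What the plan says.** Only the protocol is at hand. Its Analyses section sets the primary outcome for preterm birth of any kind: "The odds ratio of premature birth (<28/<32/<37 weeks) will be calculated between the three groups". The secondary outcomes are "Threatened premature birth, premature rupture of membranes, mode of delivery, low birth weight, admission to NICU, APGAR score, perinatal mortality".

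Among the Perined variables in Methods, two have a spontaneous category: "Start of delivery (spontaneous, iatrogenic" and "Way of delivery (spontaneous, assisted vaginal delivery, caesarean section". Perinatal death is recorded by timing and includes death before labour: "Perinatal death (gestation, antepartum/durante partu/postpartum".

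The list of plan changes, under "During data-preparation", then says: "We decided to only use the spontaneous births for our analysis". It does not say which variable defines the restriction, why it was made, or whether any outcome is exempt. The changes after peer review do not lift it. They add unadjusted analyses, the dose-response results at the two earlier cut-offs, and a quantitative measure of gestation.

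**The concern.** Exposure (CIN, biopsy, LLETZ) precedes the birth. Whether labour begins by itself or is started by a clinician is decided later, depends on the course of the pregnancy, and is settled at the moment that fixes gestational age. Selecting on it is selecting on something downstream of exposure and bound up with the outcome.

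On the plain reading (start of delivery), two kinds of birth disappear:

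- **Iatrogenic starts at term.** These women reached 37 weeks without a preterm birth. They are non-events, not ineligible.
- **Iatrogenic preterm births.** These are events under the outcome as written in Analyses.

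The Background gives a reason to doubt that the losses are equal across groups. It reports raised risks of "preterm delivery, low birth weight, premature rupture of membranes and caesarean delivery after LLETZ treatment", and both membrane rupture and caesarean delivery bear on how delivery starts.

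At stake are the meaning of the primary odds ratio, its possible bias, and the scope of the secondary outcomes.

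**Working it through.** The protocol states no preterm rate and no iatrogenic share, so there is no figure of its own to reproduce. **Every rate below is an assumption.**

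**Formula.** In group g (1 exposed, 0 control) let p be the preterm risk, a the share of preterm births excluded by the restriction, and b the share of term births excluded. Retained preterm births are p(1−a) and retained term births are (1−p)(1−b). Dividing the odds of the two groups gives

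OR(restricted) = OR(all births) × [(1−a₁)/(1−a₀)] × [(1−b₀)/(1−b₁)].

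The term-birth exclusions enter directly. The two brackets cancel to 1 when the shares are equal across groups.

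**Step 1: no true effect, a equal in both groups, b differs.**

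| Term share, exposed vs control | Restricted OR (all-births OR 1.00) |
|---|---|
| 40% vs 35% | 0.65/0.60 = 1.08 |
| 30% vs 35% | 0.65/0.70 = 0.93 |
| 35% vs 25% | 0.75/0.65 = 1.15 |
| 25% vs 35% | 0.65/0.75 = 0.87 |

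**Step 2: a real association, a differs.** Take 9% vs 6% preterm, so the all-births OR is (0.09/0.91)/(0.06/0.94) = 1.55, with equal b and a₀ = 30%.

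| a₁ | Restricted OR |
|---|---|
| 20% | 1.55 × 0.80/0.70 = 1.77 |
| 30% | 1.55 |
| 40% | 1.55 × 0.60/0.70 = 1.33 |
| 50% | 1.55 × 0.50/0.70 = 1.11 |

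**Step 3: equal shares.** With a = 30% in both groups and b equal at 10%, 25% or 40%, the OR stays 1.55. The absolute risk still moves. With 6% preterm overall it becomes 0.042/(0.042 + 0.94(1−b)) = 4.7%, 5.6% and 6.9%.

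**Step 4: all births kept in the denominator.** Count spontaneous preterm births over all births, with a = 30% in both groups: 0.7 × 6% = 4.2% and 0.7 × 9% = 6.3%. Then OR = (0.063/0.937)/(0.042/0.958) = 1.53. No term share enters, so this form does not depend on term induction practice.

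**Step 5: secondary outcomes under each reading.**

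- *Start of delivery:* planned caesareans cannot appear under mode of delivery, and antepartum deaths followed by induction drop out of perinatal mortality. The share lost is not given.
- *Way of delivery:* mode of delivery has a single level. Induced births that ended as spontaneous vaginal deliveries stay in.

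**The case against.** Spontaneous preterm birth is a defensible target, and the restriction can be read as an implicit change of outcome to it. That much stands. But a target outcome can be narrowed without deleting the other births from the denominator and from every secondary outcome, and the protocol does not say that the outcome was redefined.

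It is also true that the bias is conditional. If iatrogenic shares are equal across groups, the odds ratio is untouched, and the protocol shows no difference between groups. This limits the claim to a bias that is possible and unquantified.

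Some stronger readings are tempting but not supported:

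- **The restriction necessarily hides a membrane-rupture effect.** Assume controls with 3.0% preterm spontaneous labour, 1.5% preterm rupture and 1.5% other iatrogenic preterm birth, equal term shares, and a treatment that doubles rupture only. The planned any-preterm OR is (7.5/92.5)/(6.0/94.0) = 1.27. If 30%, 50% or 80% of rupture cases are induced and dropped, the restricted OR is 1.28, 1.22 or 1.11. Attenuation is marked only in the last case. It also requires that induction after rupture is coded as iatrogenic, which the protocol does not state.
- **Mode of delivery and perinatal mortality cannot be answered.** On the start-of-delivery reading, mode still varies (spontaneous, assisted, caesarean during labour), and intrapartum deaths, postpartum deaths and antepartum deaths with spontaneous onset remain. The outcomes are narrowed.
- **The way-of-delivery reading always loses more.** It retains some induced births, so this does not follow.
- **Adjustment for induction of labour contradicts the restriction.** That covariate belongs to the earlier plan, as twin pregnancy does. Both are leftovers that the changes supersede.

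**Conclusion.** The point holds. The restriction conditions on a post-exposure event fixed at the time of the outcome, and the resulting odds ratio does not estimate the association with premature birth as Analyses defines it.

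Whether it is biased depends on iatrogenic shares by group that the protocol does not report. Assumed term shares 5 percentage points either side of 35% move a null OR to 1.08 or 0.93, and a 10-point difference moves it to 1.15 or 0.87. A preterm share of 40% or 50% in the exposed against 30% in controls moves 1.55 to 1.33 or 1.11. These figures show sensitivity; they do not estimate the bias in this study.

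The narrowing of the secondary outcomes needs no assumed rate. Under start of delivery, planned caesareans are absent from mode of delivery, and any antepartum death followed by induction is absent from perinatal mortality. Under way of delivery, the mode outcome has one level.

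**What to change.** 1. State which variable defines *spontaneous*, why the restriction was made, and how induction after membrane rupture is classed.
2. Keep all singleton births in the denominator. Report the OR of all preterm birth at the three planned cut-offs. Beside it, report spontaneous preterm birth with iatrogenic term births as non-events and iatrogenic preterm births as a separate outcome or censored at their gestational age.
3. Analyse mode of delivery, perinatal mortality and the other neonatal outcomes on all singleton births.
4. Tabulate excluded births by group, split into preterm and term. This supplies the shares a and b, so that the bias can be judged.
5. Keep the spontaneous-only analysis as a sensitivity analysis.

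The cost is a modest re-analysis of linked data: start of delivery, way of delivery and gestation are all in the protocol's Perined variable list. Counting births induced after membrane rupture as spontaneous-type events is feasible only if the database records that sequence. Rupture is named as an outcome, but neither it nor its timing is among the listed variables.

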**Changes after peer review:**
- We included unadjusted analyses for all outcomes in the supporting information
- We included the data of the dose response relationship between increasing severity of CIN or more aggressive treatment with preterm birth of <32 weeks and <28 weeks, instead of only <37 weeks
- Instead of only dichotomized outcomes for preterm birth, we also included a quantitative measure of prematurity in days/weeks of gestation
- We divided supplementary figure 4 into a four panel graph
